### Study population

The target population (stipulated by beyondblue, the funding body) are men from the Australian farming community aged 30–64 years who self-identify as having an experience of suicide—bereaved by suicide, attempted suicide, cared for someone who has attempted suicide, had thoughts of taking their own life, or been touched by suicide in some other way. The authors recognise that all members of the rural farming community are likely to be affected by suicide to some degree and believe the Ripple Effect will have benefit beyond the target population. Given this, the primary analysis will focus on men from the farming community with an experience of suicide aged 30–64 years. However, males outside of the target age and females will not be restricted from participating in the Ripple Effect website, and will be included in secondary data analysis. Membership to the farming community will be self-identified. Participants are required to be 18 years of age of over.

### Intervention

The intervention uses a participatory approach to engage with participants informed by Kolb’s [40] experiential learning process and will be guided by a steering group comprising farmers with an experience of suicide, researchers, health professionals, farming industry representatives and digital designers. The intervention will run over a period of 8 months, preceded by a 6-week pilot program.

The Ripple Effect intervention is designed to allow access by as many isolated men (both geographically and psychologically) as possible—irrespective of the type of digital technology (or internet quality) that they have access to in their day-to-day lives. The digital platform delivering the intervention has been optimised for slow connections, and will work equally well on an old Windows PC or a new smart device. The digital platform will allow for both core and curated content to be delivered to participants. These systems will be maintained and scheduled digitally via a highly sophisticated backend. Users (de-identified) can participate anonymously, allowing them to respond in the most genuine and meaningful way possible throughout the process.

The goal of reducing suicide stigma through the Ripple Effect program will be achieved using a combination of different components within the intervention, the website:Shared stories and experiences - participants will have the opportunity to share aspects of the own story as well as read other people's messages (collected via digital Ripple Effect postcards). Postcard messages will be screened, before being digitised and included on the website, to ensure they meet the Mindframe media guidelines [41] for talking about suicide. A series of digital stories—created by members of the farming community with an experience of suicide during a professionally facilitated workshop—will be presented to participants. These stories highlight experiences of suicide stigma and how this can be overcome.Information/education – Participants will be presentation with core and curated information as they move through the website. This information covers five topics as outlined in Table 1. For each of the five topics, all participants will be presented with core content. This core content will take approximately three hours in total (across the combined topic areas) to complete. Additional curated information will be presented during the course of the intervention, depending on the nature of their experience of suicide. For example, participants who identify sexuality as influencing their experience of suicide will be delivered content on suicide risk/protective factors, tipping points and support needs specific to Lesbian, Gay, Bisexual, Transgender and Intersex (LGBTI) people.

**Table 1 Tab1:** Content of the Ripple Effect

Knowledge about suicide	Everyone’s experience is different	Talking about suicide	Recognising and maximising resources	Knowing what’s needed for keeping well
• Risk/protective factors • Warning signs • Precipitating events • Understanding suicide attempts/thoughts • Suicide stigma	• Cultural and linguistic diversity • Aboriginal and Torres Strait Islanders • Sexuality, sex and gender • Disability, illness and ageing	• Starting and managing conversations with people in distress • Crisis response • Avoiding judgement • Preparation and self-care • Talking in the community about suicide	• Positive and proactive support seeking • Knowing available resources • Overcoming barriers to support • Caring for and supporting others	• Maintaining physical, emotional, intellectual and spiritual health • Personal goal setting (evaluated us behaviourally anchored rating scale – BARS)Personal goal setting – at three set points during the intervention, participants will be invited to set SMART (Specific, Measurable, Agreed, Realistic, Time Specific) personal goals with the aim of reducing stigma. Participants will be asked to report back (within two weeks of setting the goal) on their achievement of these goals using a behaviourally anchored rating scale (BARS).Resources/support services - participants will be provided with an extensive list of resources and social and emotional wellbeing support services with national, state and local availability upon registration with the Ripple Effect.

### Study tools

#### Quantitative

The quantitative tools for assessing self-stigma and perceived-stigma have been adapted from the short form of the Stigma of Suicide Scale (SOSS) [42]. The introductory statement for the SOSS was adapted—in collaboration with the lead SOSS author [43] to focus on self-stigma and perceived-stigma. Suicide literacy was assessed using the Literacy of Suicide Scale (LOSS) [44]. The SOSS [42] and LOSS [44] have robust psychometric properties and have been validated for Australian community samples. The SOSS [42] is the only suicide attitude scale that focuses specifically on measuring stigma.

#### Qualitative

Personal insights of where stigma was/was not experienced and how stigma was overcome are measured using qualitative tools including a) questions exploring nature of suicide experience, access to support and willingness to talk about suicide; b) opportunity to complete unstructured, online ‘postcards’ of personal insights about an experience of suicide; and, c) opportunity to set unstructured personal goals and report back on these goals 7–10 days later.

#### Evaluation

Tools for evaluation will be administered in three stages (as described in Table 2):

**Table 2 Tab2:** Evaluation timeline for the Ripple Effect

Ripple Effect Evaluation measures	Pre-intervention	During intervention	Post-intervention
Demographics			
• Age	✓		
• Gender	✓		
• Location (postal code)	✓		
• Farming type	✓		
Detail of suicide experience		✓	
Suicide stigma (SOSS) [42]			
• Self-stigma	✓		✓
• Perceived-stigma	✓		✓
Suicide literacy (LOSS) [44]	✓		✓
Personal goal achievement		✓	✓
Participant feedback			✓
Qualitative interviews			✓

The initial stage of process evaluation will involve a pilot implementation of the Ripple Effect with members of the steering group. These members collectively provide extensive experience of the farming context and clinical mental health experience, and have knowledge about the aims of the Ripple Effect. Pilot participants will provide extensive online feedback via a qualitative survey as well as contribute to a group teleconference for further discussion of feedback that will be used to inform the refinement of the Ripple Effect.Following the completion of post-intervention quantitative tools (SOSS and LOSS), online feedback will be sought from the participants by way of a quantitative survey using a 7-point Likert scale, with opportunity for qualitative written comment.Follow-up semi-structured qualitative interviews with a small number of participants will investigate a) the further impact of the Ripple Effect on self-stigma and perceived-stigma, complementing and adding richness to the quantitative data in order to more clearly define what is helpful in reducing suicide stigma [12], and b) the experience of participating in the Ripple Effect.

### Data collection

Data collection will be via de-identified individualised digital interaction with participants, mapping their pattern of participation and change across time. Upon registration and prior to exposure to the intervention, participants will complete the Stigma of Suicide Scale - Short Form (SOSS) [42]—adapted to measure self-and perceived-stigma—and the Literacy of Suicide Scale (LOSS) [44].

The Ripple Effect intervention will be undertaken flexibly—participants can self-pace over a maximum 12-week period to complete the five core components. Participants are able to move in and out of the intervention as it suits them. The nature of the registration system allows for people to pick up where they left off. A personal profile page allows participants to identify their progress through the intervention. Participants will receive an email/SMS reminder if they have not logged in to the Ripple Effect after a certain period of time (determined by the participant).

On completion of all of the core content, participants will again complete the SOSS and LOSS tools (post-test). Participants who do not complete all core units will be sent an electronic reminder encouraging them to complete the post-test. Completing participants (all core content of the intervention) will be invited to participate in a semi-structured follow-up interview about their experience of participation in the Ripple Effect. A researcher with doctoral-level experience in interviewing farmers with an experience of suicide will conduct the interviews.

### Sample size

The sample size was based upon the difference in the score of the SOSS tool (pre and post-intervention). Based upon a small effect size (d = 0.2), power of 0.80 and significance level of 5% (α = 0.05), and allowing for 20% attrition, we will aim to recruit 473 participants. As was done by Taylor-Rodgers and Batterham (2014), the power calculation is conservative as it does not account for repeated measures. Purposive sampling will be used to identify 10 participants willing to contribute to the follow-up interviews.

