### Data analysis

The SOSS short form (primary outcome measure) and LOSS (secondary outcome measure) will be administered at the beginning, and following completion of the Ripple Effect as an exit survey. The comparison of pre and post data will indicate changes of both stigma and literacy variables of participants in response to the intervention. Analyses will be performed in SPSS version 23 or later. The full analysis set (FAS) will be used adhering to the intention to treat principle (ITT). This will be complemented with analysis of a per protocol set (PPS) that only includes those who have completed the core components (defined as ‘completers’—participants who have worked their way through the core content and completed pre and post measurement of stigma and literacy). Comparing the ITT with the PPS will provide a sensitivity analysis for both the SOSS and LOSS. Paired t-tests will be used to assess the effect of the intervention over time (pre- and post-Ripple Effect). In the event some participants have missing data for the post intervention assessment of SOSS and LOSS, t-tests will be replaced by a mixed model analysis using the method of residual (or restricted) maximum likelihood (REML). Supplementary analyses will include measuring changes in the SOSS and LOSS in relation to the exposure to the intervention, with exposure defined as number of core units completed. Two-sided tests will be used with a level of *p* < 0.05 determining statistical significance.

Interview data will be thematically analysed based on indications of stigma reduction, and changes in help seeking behaviours and knowledge.

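### The target of 473 adds 20% to the required number instead of dividing it by 0.8, so it covers about 16.7% attrition, not the stated 20%; the planned paired analysis is not underpowered as a result

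*Protocol article*

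**What the plan says.** The Sample size section of the protocol article names the quantity used for sizing: "The sample size was based upon the difference in the score of the SOSS tool (pre and post-intervention". It then lists the inputs, starting with "Based upon a small effect size (d = 0.2", followed by power 0.80 and a 5% level, and gives the target: "allowing for 20% attrition, we will aim to recruit 473 participants". It adds that "the power calculation is conservative as it does not account for repeated measures".

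The Data analysis section settles sidedness ("Two-sided tests will be used with a level of" p < 0.05) and the test: "Paired t-tests will be used to assess the effect of the intervention over time (pre- and post-Ripple Effect". If post-intervention scores are missing, a REML mixed model replaces the t-test. The main analysis set is the full analysis set under intention to treat; a per-protocol set of completers complements it.

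The article does not print the number required before attrition or the formula used to inflate it.

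**The concern.** A target that allows for 20% attrition should leave the required number once 20% have been lost. The printed 473 does not do this for the required number that the stated inputs imply. It looks as though 20% was added to that number, which always falls short: adding 20% and then losing 20% returns 1.2 × 0.8 = 0.96 of the starting figure.

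What is at stake is the consistency of the recruitment figure. Effect size, power, attrition allowance and target are given together as one calculation. If they do not fit, a reader cannot rely on the attrition margin that the target is said to contain.

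**Working it through.** **Inputs.** From Sample size: d = 0.2, power 0.80, α = 0.05, attrition 20%, repeated measures ignored. From Data analysis: two-sided tests. No standard deviation or pre-post correlation is given.

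**1. Reproduce the plan's figure.** With pairing ignored, the pre and post scores are treated as two independent samples. The normal approximation per sample is

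n = 2 × [(1.960 + 0.842)/0.2]² = 392.4, so 393.

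The exact t-test calculation gives 393.4, so 394. Adding 20%: 394 × 1.2 = 472.8, which rounds up to 473, the printed target.

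**2. Check that no other route gives 473.**

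| Basis | Required n | × 1.2 | ÷ 0.8 |
|---|---|---|---|
| Two samples, two-sided, t, per sample | 394 | **473** | 493 |
| Same, normal approximation | 393 | 472 | 492 |
| Same, t, both samples added | 788 | 946 | 985 |
| Paired t, two-sided | 199 | 239 | 249 |
| Two samples, one-sided, per sample | 310 | 372 | 388 |
| Paired t, one-sided | 156 | 188 | 195 |

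Only 394 × 1.2 gives 473 exactly. No basis tried comes within 3% of it by dividing by 0.8.

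**3. Correct inflation.** 394/(1 − 0.20) = 492.5, so 493, which is 20 more than 473. Check: 493 × 0.8 = 394.4.

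**4. What 473 delivers.**
- Completers after 20% attrition: 473 × 0.8 = 378.4, so 378, which is 394 − 378 = 16 short.
- Attrition actually covered: 1 − 394/473 = 0.167.
- Power of the unpaired t-test with 378 against 378: 78.4%. With 394 against 394 it is 80.1%.

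**5. What this means for the planned paired test.** Take d = 0.2 in units of the raw-score standard deviation and assume a pre-post correlation r, equal variances at both times. The standardised mean change is dz = 0.2/√[2(1 − r)]. With 378 pairs:

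| r (assumed) | dz | Power |
|---|---|---|
| 0 | 0.141 | 78.3% |
| 0.04 | 0.144 | 79.9% |
| 0.05 | 0.145 | 80.3% |
| 0.3 | 0.169 | 90.6% |
| 0.5 | 0.200 | 97.2% |

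Power passes 80% just above r = 0.04.

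**6. If the baselines of those lost are kept.** Baseline scores are collected at registration, so attrition removes only post scores. Still ignoring pairing, 473 pre against 378 post scores give 82.5% power. Power stays at 80% down to 337 post scores, a loss of 1 − 337/473 = 28.8%.

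**The case against.** The strongest reply has four parts.

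- **The 78.4% is not the power of the plan.** It discards the baselines of everyone lost, whereas the main analysis follows intention to treat and moves to a mixed model when post scores are missing. This stands. The 78.4% describes completers with pairing ignored; keeping all baselines gives 82.5% on the same unpaired footing. It limits what may be said about power, but it does not make 473 the result of allowing for a 20% loss from 394.
- **The calculation is declared conservative.** This stands for power under the paired test. The declaration concerns repeated measures, however, and says nothing about the attrition step.
- **The base of 394 is inferred.** True. The exact match at 473, and the failure of the alternatives tried, make the inference strong.
- **The effect is small.** True: 20 recruits, or 1.6 to 1.7 power points on the least favourable footing.

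A reader might infer two stronger things. One is that the trial is underpowered; the document does not support this, because the paired test clears 80% at almost any positive correlation. The other is that using an independent-samples formula for a paired test is itself a mistake; the article discloses that simplification and states its direction, so it is a choice made in the open.

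**Conclusion.** The attrition arithmetic is wrong and the rest of the calculation stands. On the stated inputs, 473 allows for about 16.7% attrition; 20% would need 493. After a 20% loss 378 completers remain against 394 required, and on completers only, with pairing ignored, power is 78.4% instead of 80%.

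This is a mis-stated figure and not a threat to the planned analysis. That judgement assumes that d is in raw-score standard deviation units, that the pre-post correlation exceeds about 0.04, and that the 473 all belong to the population analysed. The correlation is not in the document, but a value near zero would be surprising for one scale answered twice by the same person within a period of at most about 12 weeks.

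**What to change.** Keep 473 and correct its description in the Sample size section, in one of two ways:

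- state that 394 are required with pairing ignored and that 473 allows for about 16.7% attrition; or
- keep the 20% and state that it leaves 378 completers, with 78.4% power on the unpaired completers-only calculation and more under the paired test at any correlation above zero large enough to matter (80.3% at 0.05, 90.6% at 0.3, 97.2% at 0.5, all assumed values).

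Either way, printing the base of 394 lets a reader check the figure. The cost is one or two sentences. Recruitment, analysis and data collection do not change, and no extra enrolment is needed.

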### Data analysis

The SOSS short form (primary outcome measure) and LOSS (secondary outcome measure) will be administered at the beginning, and following completion of the Ripple Effect as an exit survey. The comparison of pre and post data will indicate changes of both stigma and literacy variables of participants in response to the intervention. Analyses will be performed in SPSS version 23 or later. The full analysis set (FAS) will be used adhering to the intention to treat principle (ITT). This will be complemented with analysis of a per protocol set (PPS) that only includes those who have completed the core components (defined as ‘completers’—participants who have worked their way through the core content and completed pre and post measurement of stigma and literacy). Comparing the ITT with the PPS will provide a sensitivity analysis for both the SOSS and LOSS. Paired t-tests will be used to assess the effect of the intervention over time (pre- and post-Ripple Effect). In the event some participants have missing data for the post intervention assessment of SOSS and LOSS, t-tests will be replaced by a mixed model analysis using the method of residual (or restricted) maximum likelihood (REML). Supplementary analyses will include measuring changes in the SOSS and LOSS in relation to the exposure to the intervention, with exposure defined as number of core units completed. Two-sided tests will be used with a level of *p* < 0.05 determining statistical significance.

Interview data will be thematically analysed based on indications of stigma reduction, and changes in help seeking behaviours and knowledge.

### Outcomes

The Ripple Effect’s outcomes will include:Learning and reporting about what works to reduce self-stigma and perceived-stigma associated with an experience of suicide within the farming community (as measured by the SOSS [42]).Learning and reporting about what works to increase literacy of suicide within the community of farming (as measured by the LOSS [44]).Strengthening participants’ self-perception to enable them to assist others who are suffering, thereby reducing the self-perception of shame and isolation often associated with an experience of suicide.Increasing the knowledge base of suicide and its experience, and the experience of associated stigma, in rural farming communities.Increasing the knowledge of appropriate and acceptable ways to deliver social and emotional wellbeing messaging to members of the farming community.

## Discussion

Digital media is becoming a powerful instrument for rural people in breaking down barriers of rural isolation, allowing for engagement and social interaction. The Ripple Effect utilises these opportunities to aid those with a lived experience of suicide, while also filling gaps in knowledge on the most effective experiences and processes to meaningfully shift the self-stigma and perceived-stigma associated with suicide. It is anticipated that the approach used for this study will also improve literacy of suicide in the target community. The intervention will serve as a tool to assess the extent to which digital content can alter the perceptions and feelings of individuals, with opportunities to refine and reiterate the content to further hone the most effective experiences and techniques to reduce stigma. The intervention will collect numerous data from those who use it, providing insight into the age, location and gender of all users, which content they access and how their perceptions shift. While this project is specifically focused on men aged 30-64 years, it will also be possible to track: a) men outside of this target age, and b) to what extent women use the intervention as a means of supporting their own families or partners facing a lived experience of suicide and the associated stigma. The Ripple Effect will contribute to the burgeoning knowledge of suicide stigma and literacy collected respectively by the SOSS [42] and LOSS [44] to date. Importantly, it will provide new and important knowledge about the experience of Australia’s community of farming, who have a high level of lived experience of suicide. This knowledge will inform policy, service delivery and health promotion strategies in order to more effectively support the wellbeing of rural farming communities.

### Limitations and strengths

The very nature of a digital intervention raises some study limitations. In rural areas particularly, online connectivity can be slow and of poor quality. The Ripple Effect has been designed to respond to these challenges by incorporating bandwidth optimisation for viewing images and video content. Text transcripts can also be accessed when video cannot be accessed and for participants who may be gearing impaired. Restricted access to technology will also be a potential limitation. In response to this, the Ripple Effect has been designed with optimal access from a wide range of devices—from an older desktop computer to a smart phone or tablet—to make the website accessible to as wide a range of potential participants as possible. Findings will be limited, however, to people who have access to some form of digital technology.

The farming focus of the Ripple Effect is both a limitation and a strength of the intervention. The results of this research will not be generalisable beyond the rural farming community (although may have some bearing on rural farming communities in similar contexts internationally, e.g. Canada), despite adding to the knowledge about suicide stigma and literacy in a yet unstudied population. However, this strong focus on farming provides a level of personalisation, cultural familiarity and accessibility that would not be possible in a less tailored intervention.
